**Fig 1. SPIRIT Flowchart**

|  | **STUDY PERIOD** | | | | | | |
| --- | --- | --- | --- | --- | --- | --- | --- |
|  | **Enrolment** | **Allocation** | **Post-allocation** | | | | **Close-out** |
| **TIMEPOINT*** | ***-t_1_*** | **0** | ***t_1_*** | ***t_2_*** | ***t_3_*** | ***t_4_*** | ***t_5_*** |
| **ENROLMENT:** |  |  |  |  |  |  |  |
| **Eligibility screen** | X |  |  |  |  |  |  |
| **Informed consent** | X |  |  |  |  |  |  |
| **Baseline assessment** | X | X |  |  |  |  |  |
| **Allocation** |  | X |  |  |  |  |  |
| **INTERVENTIONS:** |  |  |  |  |  |  |  |
| ***[Brief mindfulness training]*** |  |  |  |  |  |  |  |
| ***[Relaxation training]*** |  |  |  |  |  |  |  |
| **ASSESSMENTS:** |  |  |  |  |  |  |  |
| ***[Demographic data]*** | X |  |  |  |  |  |  |
| ***[Primary outcome variables]*** | X | X | X | X | X | X | X |
| ***[Secondary outcome variables]*** | X | X | X | X | X | X | X |
| ***[Daily records during intervention]*** |  | X | X |  |  |  |  |

**Fig 2. SPIRIT schedule of enrolment, interventions and assessment.**

** Note: -t1, 0, baseline; t1, post intervention; t2-t5, 6-week, 1-month, 6-month, 1-year follow-up.*

1. ***Research background. [usually adopting a four-part structure: (1) Overview of the health problem or research question: definition of the health problem, epidemiological data, etiology, natural history of the disease, disease burden, etc.; (2) Scientific hypothesis: mechanism or principle; (3) Clinical application, for example, treatment studies should explain the treatment methods; (4) Necessity of the study based on current evidence, explaining why this study needs to be conducted]***

Tobacco Use Disorder (TUD) is a pressing public health concern in China **^[1]^**, posing a significant threat to the overall well-being, and being a leading cause of death and disability of the population **^[2-5]^**. Understanding the physiological and subjective responses, such as cravings and impulses triggered by smoking cues, is crucial for comprehending the development and maintenance of addiction **^[6, 7]^**. Previous research has demonstrated that mindfulness training can influence conditioned response behaviours **^[8]^**, including reducing classical conditioning, delaying primary responses, and decreasing the frequency. Therefore, mindfulness has been widely utilized as an effective treatment for addiction and relapse prevention **^[9]^**, as it reduces subjective cravings, attentional focus, and physiological indicators associated with substance cues. By targeting negative emotions and somatic sensations, mindfulness can dissociate emotional responses from cigarette cravings **^[10]^**.

Nevertheless, the extended time commitment and the need for in-person guidance in traditional mindfulness interventions have resulted in a growing need for shorter, self-practice exercises. According to reports, even single-session mindfulness interventions and brief interventions lasting as little as 5 minutes have shown improvements in health outcomes **^[11, 12]^**. Brief mindfulness interventions have been found to reduce smokers' response to cravings **^[13]^**, improve emotional health **^[14]^**, decrease smoking consumption **^[15]^**, and have been associated with higher rates of abstinence **^[16]^**. Study in natural situation has also demonstrated that brief mindfulness training (BMT) can decrease self-reported negative emotions, smoking cravings, and cigarette consumption **^[17]^**, indicating its effectiveness in smoking cessation treatment.

Furthermore, mindfulness can influence interoceptive processing, potentially regulating brain activity related to cue-reactivity **^[9]^**. Previous research has observed functional changes in interoceptive brain regions **^[18]^**, such as the insula **^[19]^**, as well as control systems including the cingulate gyrus, parietal lobe, and prefrontal cortex **^[20, 21]^** following short-term mindfulness practice. However, there is currently a lack of in-depth research on the regulation of smoking cue responses and related brain mechanisms by brief mindfulness interventions in individuals with TUD.

Therefore, this study aims to explore the intervention effects of BMT on smoking cue-reactivity using a randomized controlled trial design. It seeks to address the limitations of long-duration mindfulness interventions with low acceptance rates among individuals with TUD and provide more targeted intervention strategies by investigating the underlying brain mechanisms. The results of this study will offer valuable insights that can enhance our understanding and support the clinical implementation of short-term mindfulness interventions in addiction treatment.

1. ***Objective***

This study aims to investigate the regulatory effects of BMT on smoking cue-reactivity by integrating subjective reports of smoking cravings with electroencephalography (EEG) data analysis. Additionally, it is dedicated to enhancing our understanding of the underlying brain processes involved and identifying potential EEG biomarkers at various timepoints.

1. ***Inclusion and exclusion criteria. [Inclusion criteria define the main body of the study and determine the representativeness of the study population; exclusion criteria define individuals within the study population that may affect the study and determine the homogeneity of the study population]***

Inclusion criteria (1) Right-handed. (2) Smoking an average of 10 or more cigarettes per day (half a pack of cigarettes). (3) Smoking history of at least 1 year. (4) Exhaled carbon monoxide (CO) levels detected by instruments are between 10-7ppm or lower (abstinent from smoking cigarette for 3 h prior to every visit). (5) Age between 18 and 40 years old. (6) Normal vision or corrected to normal vision. (7) Normal mental and physical health conditions (PHQ-9 **^[22-24]^** total score <20, GAD-7 **^[25, 26]^** total score <11). (8) Meet the diagnostic criteria for tobacco use disorder in DSM-5 (through clinical semi-structured interviews **^[27]^**).

Exclusion criteria: (1) Asthma, contact dermatitis, or allergies to silicone. (2) Recent use of corticosteroid medications within the past 3 months. (3) Practiced any meditation, yoga, tai chi, or qigong for more than 20 hours in the past year or lifetime, participated in meditation or yoga retreats, and attended any meditation courses. (4) Not suitable for EEG (e.g., metal implants, severe head trauma and electrode allergy). (5) PHQ-9 total score ≥20. (6) GAD-7 total score ≥11. (7) Adhere to specific religious beliefs and therefore unable to participate in meditation as required by the program. (8) Currently participating in similar trials or other neurophysiological experiments.

1. ***Study design, design pattern diagram, with SPIRIT template attached. [Clearly state the design scheme used in this study, such as: consecutive case or single-arm design, cross-sectional study, case-control study, cohort study, including historical cohort study or prospective cohort study, nested case-control study, randomized controlled trial, clearly specify the type, such as parallel design, crossover design, factorial design, single-group design; for treatment studies, specify the type of research objective framework, such as superiority, equivalence, non-inferiority, exploratory]***

To examine the effectiveness of brief mindfulness intervention in reducing smoking cravings, this study employs a randomized controlled parallel trial design. Expanding upon existing literature that supports the positive effects of brief mindfulness interventions, the primary aim of this study is to establish the superiority of brief mindfulness intervention over the control group within the intervention conditions. The trial consists of four distinct stages: participant recruitment, baseline measurement, measurement during the intervention period, and follow-up measurement. After the completion of each stage, pertinent evaluations will be conducted to assess the outcomes. The design flowchart, depicted in **Fig 3.**, illustrates the methodology employed in this study. It is important to note that the trial has not yet begun, and it is expected that the entire process, including participant recruitment, data analysis, and article writing, will take approximately one year. Additionally, a follow-up period of one year will be conducted to assess the long-term effects of the intervention.

**
[figure not shown]
**

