| **Affect** | -T1, T0, T1-T5 | **Positive And Negative Affect Scale（PANAS）**compiled by Watson et al. **^[39]^**, Chinese version **^[40]^** includes 10 corresponding adjectives that described either positive or negative emotion in both the both the negative and positive affect scales. Each project scores 1-5 points, with a total score of 10-50 points. to measure the emotional feelings of the past week. | secondary |
| **VAS for affect** | -T1, T0, T1-T5, during CR task | **Visual analogue scale (VAS)** for affect administered during cue-reactivity experiment to measure the state of affect, including valence and arousal. | secondary |
| **Impulsiveness** | -T1, T0, T1-T5 | **The Barratt Impulsiveness Scale Version 11 (BIS-11)** **^[41]^** was revised in 1995, consisting of a total of 30 items. The revised Chinese version **^[42]^** consists of 30 items, including three dimensions: motor impulsiveness, cognitive impulsiveness, and no planning impulsiveness, with a total score of 30-150, High scores represent hyperactivity, lack of concentration, and lack of planning, respectively. The higher the factor scores of each subscale, the stronger the impulsivity. | secondary |
| **Record of daily practice for mindfulness** | T0, T1 | Self-report of practice time; cognitive, emotional and behavioural states; course feedback and suggestions. | others |
| **Adverse events** | T0, T1-T5 | Proactive reporting without time constraints during research period. | others |
| **Socio-demographic** | -T1 | Age, gender, major, education year, Handedness | others |
| **Handedness** | -T1 | **Edingburgh Handedness Inventory（EHI）**is a measurement scale used to assess the dominance of a person’s right or left hand in everyday activities, sometimes referred to as laterality **^[43]^**, the Chinese version will be used**^[44]^**. | others |
| **Depression** | -T1 | **Patient Health Questionnaire (PHQ-9)** **^[23]^** self-administered tools for assessing depression for recent two weeks, with each project scoring 0-3 points and a total score of 0-27 points, with 6-9 points, 10-14 points, 15-21 points and 22-27 points indicating mild, moderate, severe and extreme severe depression. | others |

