| **Anxiety** | -T1 | **Generalized Anxiety Disorder (GAD-7)** used to measure anxiety related problems over the past two weeks, with each project scoring 0-3 points and a total score of 0-21 points **^[25]^**, with scores of 5, 10, and 15 corresponding to the cutoff values for "mild", "moderate", and "severe" anxiety levels **^[45]^**. | others |

*CR: cue-reactivity.

1. ***Definition of Participant Effectiveness Determination. [This includes definitions for participant withdrawal, exclusion, loss to follow-up, confounding factors, study discontinuation, and study suspension]***

(1) **Participant Withdrawal:** Each participant has the right to withdraw from the study at any time without the need to provide a reason. Participants who choose to withdraw voluntarily will not be included in the analysis. As part of our comprehensive research procedure, we have established a protocol for managing participants who decide to withdraw. If participants are willing to provide a reason for their withdrawal, it will be documented and recorded.

(2) **Participant Exclusion:** Due to the inability to ensure full intervention participation in the intervention group during the training process, the "STOP" training period lasts for one week. Participants who have participated in less than 5 training sessions will be considered as not having received the complete intervention and, theoretically, should be excluded or adjusted using mixed effects models.

(3) **Participant Loss to Follow-up:** If a participant cannot be contacted for two consecutive visits after the completion of the intervention for any reason, they will be classified as lost to follow-up.

(4) **Participant Contamination:** Following the completion of the intervention, a survey will be conducted with the participants. If the control group attempts to learn about the training mode used by the intervention group (or vice versa) and attempts to replicate the training, they will be classified as contaminated participants.

(5) **Participant Termination:** To prioritize participant health, any adverse events (including tobacco withdrawal symptoms) will be considered termination criteria. Researchers will discuss with the participant who experiencing such conditions and terminate the intervention early. Participants will receive appropriate clinical interventions only with their explicit consent.

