(3) Access and Time for Public Query of Research Plan: See the publication journal and the China Clinical Trial Registration Center and ResMan Clinical Trial Public Management Platform; 3-5 years.

1. ***Publication Plan. [Provide an estimated timeline and methods for publishing research reports. Specify the number of publications, including interim summary reports if applicable]***

(1) Estimated Time and Method for Research Report Publication: The publication plan will consist of several sections, including the research plan, analysis of panel data using various statistical methods, analysis of psychology-related data, and conclusion.

(2) Estimated Number of Publications: 1 paper (excluding interim summary reports).

1. ***Plan for Sharing Raw Data. [Describe the plan for sharing raw data with the public. Specify the maximum time frame for sharing data, which should not exceed 6 months after the end of the trial. Explain the public platform that will be used for data sharing]***

The original data will be uploaded to the ResMan Clinical Trial Public Management Platform (http://www.medresman.org.cn). The data will be publicly shared no later than 6 months after the end of the trial.

1. ***Treatment and Management of Participants after the Trial Ends. [Describe how participants who have not experienced improvement in their condition at the end of the trial will continue to receive medical care. Explain the measures that will be taken to ensure their ongoing treatment and management]***

In this study, the participants included will be healthy volunteers who will receive guidance from professional teachers in mindfulness training. The goal of this training is to assist participants in effectively managing cravings for smoking by developing skills such as paying attention to and accepting the craving when it arises, and gradually overcoming it. Additionally, this process can enhance the participants' ability to regulate their emotions when confronted with various stressful events in their daily lives.

If, upon completion of the trial, it is determined that the stress level of any participant has reached the clinical threshold, active intervention will be offered by the psychological teachers at the on-campus psychological center. If required, participants will be referred to specialized hospitals for further intervention.

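### The eligibility limits treat PHQ-9 below 20 and GAD-7 below 11 as normal mental health, but Table 1 labels part of that range severe depression and moderate anxiety; the aftercare trigger has no scheduled measure

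*Protocol*

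**What the plan says.** **Eligibility (Inclusion and exclusion criteria).** Inclusion (7) requires "Normal mental and physical health conditions (PHQ-9" with "total score <20, GAD-7" below 11). The exclusions repeat the limits from the other side: "5) PHQ-9 total score ≥20" and "6) GAD-7 total score ≥11".

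**Severity labels (Outcome Measures, Table 1).** The Depression row gives four PHQ-9 bands starting at 6, 10, 15 and 22; its last two are "15-21 points and 22-27 points indicating mild, moderate, severe and extreme severe depression" (the four labels apply to the four bands in order). The Anxiety row describes the GAD-7 "with scores of 5, 10, and 15 corresponding to the cutoff values" for mild, moderate and severe anxiety. Both questionnaires are scheduled at -T1 only.

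**Description of participants and aftercare (Treatment and Management of Participants after the Trial Ends).** This section states that "the participants included will be healthy volunteers". It then offers intervention by the campus psychological centre, with referral if needed, when it is found at completion that "the stress level of any participant has reached the clinical threshold". It names no instrument and no value.

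**The concern.** Inclusion (7) states its own purpose, which is to secure normal mental health. The two scores in its bracket are the only operational definition given. On the protocol's own bands, those scores do not deliver that purpose.

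Two things are at stake.

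- **Description of the population.** A report that repeats the words normal or healthy would misdescribe who was eligible.
- **Safety oversight.** The adverse-events section lists anxiety and depression among the withdrawal symptoms that staff ask about daily. The section on participant effectiveness makes any adverse event, withdrawal symptoms included, a criterion for termination. A student who enters with a high PHQ-9 score may report symptoms that were there before training began, and no second PHQ-9 score is planned to compare with the first. At the end of the trial, the offer of help depends on a threshold that the protocol neither defines nor schedules a scale for.

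**Working it through.** The protocol gives no figure to reproduce. The check compares the eligible score ranges with the Table 1 labels.

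**PHQ-9.** Inputs: total score 0 to 27 and bands 6-9, 10-14, 15-21 and 22-27 (Table 1); eligible below 20, excluded from 20 upwards (inclusion (7), exclusion (5)).

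| Table 1 label | Scores | Eligible | Excluded |
| --- | --- | --- | --- |
| none given | 0-5 | 0-5 (6 of 6) | none |
| mild | 6-9 | 6-9 (4 of 4) | none |
| moderate | 10-14 | 10-14 (5 of 5) | none |
| severe | 15-21 | 15-19 (5 of 7) | 20-21 (2 of 7) |
| extreme severe | 22-27 | none | 22-27 (6 of 6) |

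Sum check: 6 + 4 + 5 + 5 = 20 eligible values (0-19) and 2 + 6 = 8 excluded values (20-27), 28 in all. The boundaries between bands lie at 6, 10, 15 and 22. The limit of 20 matches none of them and splits the severe band.

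**GAD-7.** Inputs: total score 0 to 21 with cut-offs 5, 10 and 15 (Table 1); eligible below 11 (inclusion (7), exclusion (6)). Eligible scores are 0-10. They include all of 5-9, which starts at the mild cut-off, and the single value 10, which is the moderate cut-off.

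**Does another criterion close the gap?** No. The semi-structured interview in inclusion (8) serves the diagnosis of tobacco use disorder. History of mental illness is recorded under Baseline measures and observed variables but is not an exclusion. A student with a PHQ-9 of 15-19 must also have a GAD-7 below 11; this narrows the group but does not remove it.

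**Aftercare trigger against the schedule.** The trigger is a stress level assessed at completion. Table 1 has no stress scale. The two scales in Table 1 that carry severity cut-offs for depression and anxiety are taken at -T1 only. PANAS (affect) and adverse events are followed to T5, but Table 1 gives neither a clinical threshold.

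**The case against.** **The rule itself is clear.** The inclusion and exclusion limits agree exactly, so screeners would apply one rule, and in this protocol the Table 1 bands drive no eligibility, analysis or stopping decision. This stands: the conflict lies between the limits and the labels. It still matters, because the rule states a purpose that it does not meet on the protocol's own bands.

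**Healthy volunteers is loose wording.** Every participant must meet criteria for tobacco use disorder, so the phrase cannot be meant strictly. That is fair, and the phrase is weaker evidence than inclusion (7). The GAD-7 part is also marginal, since it turns on one score value.

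**A reader might infer that severely depressed students will be enrolled.** The documents do not support this. They give no score distribution, the label applies to a self-report score, and the Table 1 bands may be the part that needs correcting. For the same reason, counts of score values say nothing about shares of participants.

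**A reader might infer that the aftercare offer can never be triggered.** This too goes too far. The adverse-events section allows identification by self-report, observation, examination and medical records, and the participant management section provides an emergency team that participants can contact at any time. What is missing is a defined threshold and a scheduled measure.

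**A reader might infer that depression and anxiety add variation that the analysis ignores.** Statistical analysis methods adjusts for individual factors and pre-intervention variables and names two only as examples. The PHQ-9 and GAD-7 are already baseline indicators, and the exact covariate list may be in the analysis plan. No fault is shown there.

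**Conclusion.** The inconsistency is real, and nothing else in the protocol resolves it. PHQ-9 scores of 15-19 (5 of the 7 values in the severe band) and a GAD-7 score of 10 count as normal mental health for eligibility but as severe and moderate in Table 1. Separately, the aftercare commitment rests on an undefined threshold with no scheduled measure behind it.

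The conclusion assumes only that the Table 1 bands and the eligibility limits are both meant as printed. It does not depend on which of them is clinically right, and no view is taken on that. The number of participants affected cannot be derived from the documents. No effect on power or error rate and no bias in the randomised comparison is shown. The consequences concern who may be enrolled, how they are described and how they are looked after. The point should be settled before enrolment.

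**What to change.** 1. Before enrolment, the clinical team reconciles three items so that they agree: the eligibility limits (Inclusion and exclusion criteria), the severity bands (Table 1, Depression and Anxiety rows) and the words normal and healthy volunteers (inclusion (7); Treatment and Management of Participants after the Trial Ends). Whether the limits, the bands or the wording should change is a clinical decision, and none is proposed here.
2. The team also reconciles the aftercare trigger with the assessment schedule, so that the text and the planned measurements match. Repeating the PHQ-9 and GAD-7 would not settle this by itself, because they measure depression and anxiety while the trigger refers to stress.
3. Optional: name baseline PHQ-9 and GAD-7 among the pre-intervention covariates in Statistical analysis methods. Both are already collected at -T1.

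**Cost.** Items 1 and 2 need amended wording. The Study design section says the trial has not begun, so no enrolled participant is affected. If the team changes a limit, recruitment may slow; the documents do not allow an estimate. Item 3 costs two degrees of freedom, if each score enters as one linear term, and no new data collection.

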**Fig 3. Study Design and Procedure**

*The upper portion of the figure illustrates the overall study design. The middle portion depicts the timeline for assessing scales and EEG at baseline, post-intervention, and follow-up timepoints. Brief mindfulness and relaxation training will be administered to both the intervention and control groups after recruitment. The baseline assessment (-T1, T0) will be completed before the intervention. Audio guidance will be provided for daily practice in the BMT group, while there will be no additional practice or intervention for the control group after training. The lower portion of the figure represents the modules of psychological and behavioural assessments during the baseline and five follow-up sessions. The cue-reactivity task will be implemented using a customized two-choice oddball paradigm. INT: intervention, rs-EEG: resting-state EEG; BMT: brief mindfulness training; VAS: Visual analogue scale; SMT: state-mindfulness.*

1. ***Sample size estimation. [List the four elements: δ(Δ) or π1, π2, α, β or Power, and provide the calculation formula]***

In this study, the subjective reports of smoking urges (QSU-Brief) will be used as the primary outcome measure. Referring to study of similar populations **^[28]^**, We set δ(Δ)_tot_ = 4 to represent the anticipated reduction of 4 points in the QSU-Brief score after the intervention in the experimental group. Multiple measurements of the QSU-Brief will be conducted on participants before and after the training, as well as during the 60-minute online training period. To estimate Cohens’d, we have set α = 0.05 and β = 0.80. Cohens’d can be calculated using the formula Cohens’d=(δ(Δ)/SD_estimate_), where the estimated SD_estimate_ was 7.65 based on reference study. Therefore, the corresponding command is pwr.t.test (d=cohens_d, sig.level = 0.05, power = 0.80, type = "paired", alternative = "two.sided"), and the estimated sample size is 34. Therefore, the minimum required sample size for the experimental group is 34. Considering a natural dropout rate of 30%, the sample size for the experimental group should be no less than 45.

1. ***Methods of randomization and concealed allocation. [Randomization is used to reduce the risk of selection bias. Methods for generating random number sequences include computer software, random number tables, semi-random or pseudo-random methods (such as using dates, birthdays, or even/odd numbers of hospital visits). Please describe the individuals involved in generating random number sequences and the methods they use. Concealed allocation is used in treatment studies to reduce the risk of selection bias. Key steps in concealed allocation include having a designated person determine the allocation sequence, ensuring that this person is not involved in enrolling participants, and securely storing the allocation table. Please provide detailed descriptions of these steps. Central randomization is a robust method of concealed allocation. Describe the individuals and methods involved in determining the allocation sequence]***

(1) In this study, the intervention period for the BMT, which is a behavioural training, lasts for one week. Baseline data, including EEG data, will be collected from all participants. Following this, there will be a one-week training period for the intervention content, after which post-intervention data, including scales, self-reports, and EEG data, will be collected. Follow-up measurements will be conducted at 1 week, 1 month, 3 months, 6 months, and 1 year after the trial's completion. Group allocation will be performed after the completion of baseline data collection.

(2) The primary intervention method employed in this study is the brief mindfulness-based intervention of "STOP" **^[29, 30]^**, with a 7-day ~60-min sessions mindfulness course for the experimental group. Meanwhile, the control group will undergo relaxation training. All recruited participants are from the same school, and due to the lack of blinding execution conditions, achieving double-blind standards may present challenges.

(3) The randomization process for this trial will involve the use of a random sequence generator website (https://www.random.org/). This website will be utilized to ensure the random assignment of participants to either the experimental or control group.

1. ***Blinding. [Blinding is used in treatment studies and diagnostic trials to reduce the risk of implementation bias and measurement bias. Implementing strict confidentiality measures, such as using placebos or simulating procedures, is an effective blinding method. If blinding is necessary and feasible for your study, describe the methods and procedures for implementing blinding]***

This trial includes group therapy sessions for students from the same school. As a result, participants may already know each other or be unfamiliar with one another, and they may naturally discuss the experimental training they receive. Maintaining blinding for the researchers is challenging as they may be influenced by the experimental content during the trial. Therefore, meeting the requirements of double-blinding in a clinical trial is not feasible in this situation

1. ***Outcome Measures. [Outcome measures are used to evaluate the results of a study and can include primary, secondary, and safety measures, including adverse events and reactions. Please describe the names of the measures, the methods of measurement, and the time points at which they are assessed]***

As listed in **Table 1**, the primary outcomes include subjective reports of smoking craving, changes in EEG indicators, and mindfulness measures (both trait- and state- mindfulness). The secondary outcomes will be daily smoking behaviours (number of cigarettes smoked per day, exhaled carbon monoxide concentration), affect and impulsivity, as well as indicators reflecting correlation between mindfulness and smoking cue-reactivity. Researchers will inquire daily during the intervention period whether participants experience tobacco withdrawal symptoms or any other adverse reactions. Participants are also encouraged to proactively contact the research team if they experience any adverse reactions. Please refer to item 9 for the time points of assessment.

| **Table 1. Evaluated variables** | | | |
| --- | --- | --- | --- |
| **Variables** | **Timepoints** | **Measures** | **Outcome level** |
| **Category 1: smoking related indices** | | | |
| **Nicotine dependence** | -T1, T0, T1-T5 | **Fagerstrőm test for nicotine dependence (FTND)** is a six-item revision of the Fagerstrőm Tolerance Questionnaire **^[31]^**，scored as 0-3 (low), 4-6 (moderate), and 7-10 (high) with the summed score **^[32]^**. | primary |
| **Craving** | -T1, T0, T1-T5 | **1.Tobacco Craving Questionnaire-Short Form (TCQ-SF**）is short form of 12 optimized projects to assess smoking craving levels，including four factors of emotionality, expectancy, compulsivity, and purposefulness **^[33]^**, with each factor scores from 3 to 21 points, was used in Chinese population**^[34]^**. | primary |
|  |  | **2.Questionnaire on Smoking Urges-Brief（QSU-Brief）**developed by Cox et al., **^[35]^** suitable for multiple measurements in laboratory and clinical use, including 10 items, can be completed in less than 2 minutes. Each item uses a subjective score of 1-7 points to evaluate the current level of craving for tobacco, the Chinese version will be adopted **^[36]^**. |  |
| **VAS for craving** | -T1, T0, T1-T5, during CR task | **Visual analogue scale (VAS)** administered during cue-reactivity experiment to measure the state of craving, responses to each item were rated using a scale that ranged from 0 (not at all) to 10 (the strongest feeling possible). | primary |
| **Number of cigarettes smoked per day** | -T1, T0, T1-T5 | Self-report for number of cigarettes smoked per day. | secondary |
| **Exhaled carbon monoxide (CO)** | T0, T1-T5 | Instantaneous reading device (Bedfont piCO Smokerlyzer) used to identify whether the duration of cigarette cessation meets the requirements. | secondary |
| **Category 2: mindfulness** | | | |
| **Trait-mindfulness** | T0, T1-T5 | **Five Facet Mindfulness Questionnaire（FFMQ）**consisting of 39 items and 5 factors, namely observation, description, acting with awareness, non-reactivity, and non-judging, the Chinese version will be used**^[37]^**. | primary |
| **State-mindfulness** | T0, T1-T5, during CR task | Based on the Toronto Mindfulness Scale (TMS), two items in Chinese version **^[38]^** were used to evaluate the dimensions of curiosity and decentralization. | primary |
| **Category 3: brain function** | | | |
| **Brain function** | T0, T1-T5 | Using a 64-channel EEG system to record in both resting and experimental conditions. | primary |
| **Category 4: Socio-demographic and clinical information** | | | |
| **Self-emotional assessment** | T0, T1 | **Self-assessment manikin (SAM)** used to measure the emotional state during 7-day mindfulness intervention. | others |
| **Affect** | -T1, T0, T1-T5 | **Positive And Negative Affect Scale（PANAS）**compiled by Watson et al. **^[39]^**, Chinese version **^[40]^** includes 10 corresponding adjectives that described either positive or negative emotion in both the both the negative and positive affect scales. Each project scores 1-5 points, with a total score of 10-50 points. to measure the emotional feelings of the past week. | secondary |
| **VAS for affect** | -T1, T0, T1-T5, during CR task | **Visual analogue scale (VAS)** for affect administered during cue-reactivity experiment to measure the state of affect, including valence and arousal. | secondary |
| **Impulsiveness** | -T1, T0, T1-T5 | **The Barratt Impulsiveness Scale Version 11 (BIS-11)** **^[41]^** was revised in 1995, consisting of a total of 30 items. The revised Chinese version **^[42]^** consists of 30 items, including three dimensions: motor impulsiveness, cognitive impulsiveness, and no planning impulsiveness, with a total score of 30-150, High scores represent hyperactivity, lack of concentration, and lack of planning, respectively. The higher the factor scores of each subscale, the stronger the impulsivity. | secondary |
| **Record of daily practice for mindfulness** | T0, T1 | Self-report of practice time; cognitive, emotional and behavioural states; course feedback and suggestions. | others |
| **Adverse events** | T0, T1-T5 | Proactive reporting without time constraints during research period. | others |
| **Socio-demographic** | -T1 | Age, gender, major, education year, Handedness | others |
| **Handedness** | -T1 | **Edingburgh Handedness Inventory（EHI）**is a measurement scale used to assess the dominance of a person’s right or left hand in everyday activities, sometimes referred to as laterality **^[43]^**, the Chinese version will be used**^[44]^**. | others |
| **Depression** | -T1 | **Patient Health Questionnaire (PHQ-9)** **^[23]^** self-administered tools for assessing depression for recent two weeks, with each project scoring 0-3 points and a total score of 0-27 points, with 6-9 points, 10-14 points, 15-21 points and 22-27 points indicating mild, moderate, severe and extreme severe depression. | others |
| **Anxiety** | -T1 | **Generalized Anxiety Disorder (GAD-7)** used to measure anxiety related problems over the past two weeks, with each project scoring 0-3 points and a total score of 0-21 points **^[25]^**, with scores of 5, 10, and 15 corresponding to the cutoff values for "mild", "moderate", and "severe" anxiety levels **^[45]^**. | others |

*CR: cue-reactivity.

1. ***Definition of Participant Effectiveness Determination. [This includes definitions for participant withdrawal, exclusion, loss to follow-up, confounding factors, study discontinuation, and study suspension]***

(1) **Participant Withdrawal:** Each participant has the right to withdraw from the study at any time without the need to provide a reason. Participants who choose to withdraw voluntarily will not be included in the analysis. As part of our comprehensive research procedure, we have established a protocol for managing participants who decide to withdraw. If participants are willing to provide a reason for their withdrawal, it will be documented and recorded.

(2) **Participant Exclusion:** Due to the inability to ensure full intervention participation in the intervention group during the training process, the "STOP" training period lasts for one week. Participants who have participated in less than 5 training sessions will be considered as not having received the complete intervention and, theoretically, should be excluded or adjusted using mixed effects models.

(3) **Participant Loss to Follow-up:** If a participant cannot be contacted for two consecutive visits after the completion of the intervention for any reason, they will be classified as lost to follow-up.

(4) **Participant Contamination:** Following the completion of the intervention, a survey will be conducted with the participants. If the control group attempts to learn about the training mode used by the intervention group (or vice versa) and attempts to replicate the training, they will be classified as contaminated participants.

(5) **Participant Termination:** To prioritize participant health, any adverse events (including tobacco withdrawal symptoms) will be considered termination criteria. Researchers will discuss with the participant who experiencing such conditions and terminate the intervention early. Participants will receive appropriate clinical interventions only with their explicit consent.

(6) **Participant Suspension:** Participants in this study can request to suspend the intervention. If a suspension is requested, the participant will be evaluated by the study team and, if approved, moved to the future intervention group. Data collected before the suspension will not be included in the final data analysis.

1. ***Definition, identification methods, and management systems for adverse events and reactions.***

In the "Chinese Clinical Smoking Cessation Guidelines," it is stated that smokers may experience a range of withdrawal symptoms after quitting or reducing smoking. These symptoms include smoking cravings, anxiety, depression, restlessness, headache, increased salivary gland secretion, lack of concentration, and sleep disorders. Withdrawal symptoms typically begin within hours of smoking cessation, peak within the first 14 days, and gradually diminish until they disappear. Most withdrawal symptoms last for about one month, although some patients may experience cravings for smoking for over a year.

**Definition:** Adverse events refer to any unfavorable or unintended signs, symptoms, or diseases that occur during or after the intervention, regardless of whether they are related to the intervention. Adverse reactions specifically refer to unfavorable or unintended responses that are causally related to the intervention.

**Identification Methods:** Adverse events and adverse reactions can be identified through various methods, including participant self-reporting, researcher observations, physical examinations, laboratory tests, and medical records.

**Management System:** In light of the potential adverse reactions mentioned above, the researchers will conduct daily inquiries during the intervention to determine whether participants have experienced any of the symptom. The delivered list will also provide information to participants, instructing them to promptly contact the researchers if they experience similar symptoms at any other time. In the event of any adverse reactions, responsible personnel from the medical school and psychology department will promptly contact the participants and assess their psychological and physiological conditions. Based on the participant's willingness, a collective decision will be made by the medical school, psychology department, and participant regarding their continued participation in the subsequent research. The researchers will record the reasons for their decision.

